#### Barriers and enablers of implementation

Participants in the intervention group will be invited to an interview or focus group to discuss their user experience and to provide suggestions for further improving the app. These qualitative interviews are an integral component of the process evaluation and will help identify barriers and enablers to implementation. Semi-structured interviews will be conducted by a bilingual researcher, guided by a pre-established interview guide (online supplemental file 1). The interviews will be audio-recorded and analysed using directed content analysis. Maximum variation sampling will be used to obtain a range of views.

### Statistical analysis

Statistical analysis will follow the intention-to-treat principle and a prespecified statistical analysis plan led by a blinded statistician. Descriptive statistics will be used to characterise participants. The analysis of variance (ANOVA) will be used to compare the primary outcome and estimate the mean difference and 95% CI. Furthermore, to assess whether there is a change in the outcome over time (baseline, 1 month and 3 months) within and between groups, a linear mixed effects regression model will be used with a random intercept for patients to account for individual variability. Assumptions for ANOVA and the linear mixed-effects model will be assessed prior to analysis. For ANOVA, independence, normality within groups and homogeneity of variances will be checked using Levene’s test, and outliers will be addressed if necessary. For the mixed-effects model, linearity, residual normality and homoscedasticity will be evaluated through diagnostic plots. If assumptions are violated, corrective measures such as data transformation or robust methods will be applied. In the case of missing data that are missing at random in nature, multiple imputations will be used. For secondary continuous outcomes, linear mixed effects regressions will be performed to assess whether there is change in the outcomes over time within and between groups. Similarly, for secondary categorical outcomes, mixed effects logistic regression models will be used to test for the change in the outcomes over time within and between groups.

Interview audio files will be transcribed verbatim into simplified Chinese and then translated into English by a bilingual researcher. To ensure the accuracy and reliability of the translation, another bilingual author will randomly audit five translated transcripts and back-translate these from English into simplified Chinese. The data will then be analysed using directed content analysis, with coding and theme generation facilitated by an Excel spreadsheet.

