**Methods and analysis:**

This multicentre, assessor-blinded, randomised controlled trial will recruit 98 Chinese-speaking inpatients following ACS with evaluation at 1 and 3 months postdischarge. Control participants in the control group will receive the usual ward-based patient discharge education. Intervention participants will additionally receive the education app installed on their devices before hospital discharge with unlimited access during the study period. Cultural relevance and linguistic accuracy for this Chinese version of an existing app were ensured through co-adaptation with Chinese-speaking consumers; the primary outcome will be coronary heart disease (CHD) knowledge, and secondary outcomes will include knowledge, attitudes and beliefs regarding heart attack symptoms and responses, CHD self-management behaviours, utilisation of healthcare services and quality of life. A process evaluation will be conducted alongside the trial to assess the acceptability and feasibility of the app. Between-group comparisons will be made using 95% CIs, accounting for baseline differences using linear mixed effects or mixed effects logistic regression models.

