### Data collection and study outcomes

Assessments will occur at baseline and 1 and 3 months after hospital discharge through phone interviews conducted by a researcher, as listed in table 1.

**Table 1 T1:** Study outcomes and assessment time point

Study outcome	Measurement	Baseline	1 month	3 months

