**Primary outcome**				
CHD knowledge	CADE-Q SV (Simplified Chinese)	✓	✓	✓
Knowledge, attitudes and beliefs about heart event	C-ACSRI	✓	✓	✓

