**Other secondary outcomes**				
Cardiac-related mortality	Family reported		✓	✓
Quality of life	EQ-5D-5L	✓		✓
App acceptability	App user survey		✓	
App feasibility	Data analytics			✓
Barriers and facilitators of implementation	Individual interview and focus group			✓

C-ACSRI, Chinese version of Acute Coronary Syndrome Response Index; CADE-Q SV, short version of the Chinese-language Coronary Artery Disease Education Questionnaire; CADSMS, Coronary Artery Disease Self-Management behaviour Scale; CHD, coronary heart disease; EQ-5D-5L, Five-Level EuroQol five-dimension instrument.

The primary outcome will be the mean difference between intervention and control groups in CHD knowledge scores and knowledge, attitudes and beliefs about heart attack symptoms and responses. Key secondary outcomes will include CHD self-management behaviours, cardiac-related hospital admission and use of healthcare services. Other secondary outcomes will include cardiac-related mortality, quality of life, app acceptability, app feasibility and barriers and facilitators of implementation.

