### Sample size calculation

Since there is no established minimally important difference in disease knowledge or similar intervention for the CADE-Q SV (Simplified Chinese), the sample size calculation is based on a mean change of 2.3 points (SD 3.6), which has been published in patients with CHD precompleting and postcompleting a comprehensive cardiac education programme.^41^ A total of 78 participants (39 per group) will be required to detect a between-group difference in CADE-Q SV (Simplified Chinese) score of 2.3 points with (α=0.05, 80% power) (calculated from https://sample-size.net/sample-size-means/). Accounting for a 20% dropout rate, 98 patients (49 per group) will be needed.

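### The body gives the primary CADE-Q SV comparison to an ANOVA with no stated baseline term, while the abstract promises baseline-adjusted mixed models; reconcile the two and use the baseline score

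*Protocol article*

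**What the plan says.** In the protocol article, the Statistical analysis section assigns the primary result to one method: "The analysis of variance (ANOVA) will be used to compare the primary outcome and estimate the mean difference and 95% CI". No baseline covariate is mentioned, and the assumption checks listed for the ANOVA are those of a plain group comparison. The section then adds a linear mixed model of the same outcome with a random patient intercept, "to assess whether there is a change in the outcome over time (baseline, 1 month and 3 months) within and between groups".

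The abstract (Methods and analysis) describes the between-group analysis differently and does not mention ANOVA: "Between-group comparisons will be made using 95% CIs, accounting for baseline differences using linear mixed effects or mixed effects logistic regression models".

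The baseline score will be available. The section on data collection states: "Assessments will occur at baseline and 1 and 3 months after hospital discharge", and Table 1 ticks CADE-Q SV at all three times. The text below Table 1 defines the outcome on scores rather than on changes: "The primary outcome will be the mean difference between intervention and control groups in CHD knowledge scores". It does not name a deciding visit.

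**The concern.** The abstract and the body describe different routes to the trial's main estimate, one accounting for baseline and one apparently not. A reader of the published article cannot tell which will be reported as the primary result.

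Precision is also at stake. A patient's knowledge score before the intervention is likely to predict the score afterwards. Leaving it out puts that predictable variation into the error term, so the confidence interval is wider than the same data allow. The cost depends on the correlation between baseline and follow-up scores, which the article does not give, and on what the SD in the sample size section refers to.

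**Working it through.** **Inputs from the Sample size calculation section.** Difference 2.3 points, SD 3.6, "α=0.05, 80% power", 39 per group evaluable, 20% dropout, 98 in total.

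**Assumed, not in the article.** The correlation r between baseline and follow-up CADE-Q SV, taken as 0.3, 0.5 or 0.7.

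**Step 1: reproduce the plan's figure.** The two-sided normal formula is n per arm = 2 × (1.96 + 0.84)² × SD² / difference². With 3.6 and 2.3 this gives 38.5, rounded up to 39 per arm and 78 in total. Inflating, 78 / 0.8 = 97.5, so 98. The plan's numbers reproduce, and they are those of an unadjusted two-group comparison. The exact t-test power at 39 per arm is 79.5% (80.5% by the normal approximation).

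**Step 2: 3.6 read as the SD of the follow-up score.** Residual SD after adjustment = 3.6 × √(1 − r²). CI half-width = 1.99 × residual SD × √(2/39). Power is from the t-test at 39 per arm, ignoring the one degree of freedom spent on the covariate.

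| r | Residual SD | Power | CI half-width (points) |
|---|---|---|---|
| Unadjusted | 3.60 | 79.5% | 1.62 |
| 0.3 | 3.43 | 83% | 1.55 |
| 0.5 | 3.12 | 90% | 1.41 |
| 0.7 | 2.57 | 97% | 1.16 |

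**Step 3: 3.6 read as the SD of change.** The section says "the sample size calculation is based on a mean change of 2.3 points (SD 3.6" and takes these figures from a before-and-after comparison, so this reading is open. If the score has the same SD at baseline and follow-up, score SD = 3.6 / √(2(1 − r)), and the adjusted residual SD is that value × √(1 − r²).

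| r | Score SD | Power, ANOVA of follow-up scores | Adjusted SD | Power, adjusted |
|---|---|---|---|---|
| 0.3 | 3.04 | 91% | 2.90 | 93% |
| 0.5 | 3.60 | 80% | 3.12 | 90% |
| 0.7 | 4.65 | 58% | 3.32 | 86% |

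On this reading the unadjusted analysis drops below the planned 80% once r exceeds 0.5, while the adjusted analysis stays at 86% or more over the range. At r = 0.3 there is little to choose between them.

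**The case against.** The strongest reply is that the body is not truly ambiguous. ANOVA is given the mean difference and its interval, and the mixed model is introduced as a further step about change over time. The natural reading is therefore ANOVA primary and mixed model supportive, with the abstract compressing all outcomes into one sentence. This largely stands. A reader might infer two rival primary analyses with nothing to decide between them, but the Statistical analysis section does not go that far. What remains is the abstract's statement, which assigns between-group comparisons only to baseline-accounting mixed models and so does not match the body.

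A second reply is that an unadjusted ANOVA is sound under 1:1 randomisation. It is unbiased, and its interval already allows for chance imbalance at baseline. That stands in full. It would be wrong to infer that the primary result is biased, or that the trial is underpowered on its stated inputs: if 3.6 is a follow-up SD, the ANOVA delivers about the planned 80%.

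Third, the article refers to a prespecified analysis plan that is not shown and may give covariates and a visit. Nowhere does the article say that the ANOVA uses a single visit, so a charge that it discards a follow-up visit would be inference. Nor is dropout ignored: multiple imputation is planned and the sample size is inflated. The missing detail is therefore not the point. The point is that the article itself describes the between-group analysis in two ways, which an unseen plan cannot cure in the published text.

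Finally, the ANOVA might be meant on change scores, which would use baseline. The outcome is defined on scores, however, and adjustment for baseline would be at least as precise.

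**Conclusion.** The concern holds as a mismatch to be reconciled and as precision forgone, not as an invalid analysis. The body names an ANOVA without a baseline covariate; the abstract promises comparisons that account for baseline; the baseline score is collected in any case.

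The size of the gain is conditional. It rests on an assumed correlation of 0.3 to 0.7 and on how the SD of 3.6 is read. With a follow-up SD, adjustment adds roughly 4 to 18 percentage points of power and narrows the interval by about 5% to 29% (1.62 to 1.55, and 1.62 to 1.16). With a change SD and equal variances over time, it adds from about 2 points (r = 0.3) to about 28 points (r = 0.7). Only in this second case, with r above 0.5, would the ANOVA of follow-up scores fall short of the planned power.

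**What to change.** Name one baseline-adjusted primary analysis of CADE-Q SV. Either ANCOVA at the chosen visit, or a mixed model of the 1- and 3-month scores with the baseline score as covariate (or with baseline means constrained equal across groups), would serve.

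State one deciding contrast at one named visit. A mixed model with a group-by-visit term yields a contrast at each visit and an average, so naming the model alone would still leave a choice. Report the adjusted difference in points with its 95% CI, and label the unadjusted ANOVA as a sensitivity analysis.

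Use the same wording in the abstract, the Statistical analysis section and the analysis plan, and say whether 3.6 is the SD of a score or of a change. The change should be fixed before anyone sees outcome data by group. It costs wording only: no extra patients, visits or measurements, and the sample size of 98 can stay.

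### The random-intercept model for the three-visit outcomes can give a miscalibrated confidence interval for the between-group difference in change; an unstructured covariance would avoid this at little cost

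*Protocol article*

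**What the plan says.** The Statistical analysis section of the protocol article describes two analyses of the primary outcome. The first is cross-sectional: "The analysis of variance (ANOVA) will be used to compare the primary outcome and estimate the mean difference and 95% CI". The second is added to it. In order "to assess whether there is a change in the outcome over time (baseline, 1 month and 3 months) within and between groups", the section says that "a linear mixed effects regression model will be used with a random intercept for patients to account for individual variability". It states no random slope and no residual covariance.

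The listed checks for the mixed model are that "linearity, residual normality and homoscedasticity will be evaluated through diagnostic plots". The remedy follows: "If assumptions are violated, corrective measures such as data transformation or robust methods will be applied". The section also refers to "a prespecified statistical analysis plan led by a blinded statistician", which is not at hand.

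The abstract gives the mixed models a larger role. It says that between-group comparisons use 95% CIs, "accounting for baseline differences using linear mixed effects or mixed effects logistic regression models".

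In Table 1 the two continuous outcomes with all three visits are the CADE-Q SV knowledge score and the Chinese ACS Response Index. Self-management behaviour and EQ-5D-5L are measured at baseline and 3 months only.

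**The concern.** A random intercept with independent residuals is compound symmetry: one variance at all visits and one correlation for all pairs of visits. The model then estimates a single error variance for every change and applies it to the baseline-to-3-month contrast, whatever that contrast's own variance is.

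The design gives reason to doubt equal correlation. Under Setting and recruitment, baseline is completed before randomisation. Under Intervention, the app is installed afterwards and used as each participant chooses. Under App feasibility, the investigators plan to measure module completion and frequency of access, both of which can differ between patients. Differences in what patients learn would be shared by the 1-month and 3-month scores and absent at baseline. Baseline and 3 months are also the pair furthest apart in time.

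If so, the model borrows precision from the tight 1-to-3-month pair and reports too small a standard error for the 3-month change. At stake is the false-positive rate, and the honesty of the interval, for the between-group change in the knowledge score and the ACS Response Index.

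**Working it through.** **Inputs from the article (Sample size calculation).** Difference 2.3 points, SD 3.6, α = 0.05, power 80%, 39 per group evaluable, 20% dropout.

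**The plan's own figure.** n per group = 2 × (1.960 + 0.842)² × 3.6² / 2.3² = 38.5, so 39 per group and 78 in total. Then 78 / 0.8 = 97.5, so 98. The stated sample size reproduces (a t-based calculation gives 40 per group) and is not affected by this point.

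**Assumptions.** The article gives no correlation between visits, so every correlation below is assumed. The SD of 3.6 is published for a pre-to-post change; it is used here as the SD at each visit. With equal SDs it scales the standard errors but cancels from the error rates.

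**Formulas.** Take complete, balanced data and a group-by-visit model with visit as a category.
- Variance of a within-patient difference between visits j and k, with equal SDs: D(j,k) = 2 × 3.6² × (1 − ρ) = 25.92 × (1 − ρ).
- Random-intercept variance of the group difference in 3-month change: (2/39) × M, where M is the mean of the three D values.
- Correct variance: (2/39) × D(0,3).
- Ratio of model SE to correct SE: R = √(M / D(0,3)).
- Type I error ≈ 2 × [1 − Φ(1.96 R)].

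**Worked case 0.5, 0.5, 0.7** (order: baseline–1 month, baseline–3 months, 1–3 months). D(0,1) = 12.96, D(0,3) = 12.96, D(1,3) = 7.776, so M = 11.232. Model SE = √(2 × 11.232 / 39) = 0.759. Correct SE = √(2 × 12.96 / 39) = 0.815. R = 0.931 and type I error = 6.8%.

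**All cases, 3-month change:**

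| Correlations | M | D(0,3) | Model SE | Correct SE | R | Type I error |
|---|---|---|---|---|---|---|
| 0.5, 0.5, 0.5 | 12.960 | 12.960 | 0.815 | 0.815 | 1.00 | 5.0% |
| 0.5, 0.45, 0.6 | 12.528 | 14.256 | 0.802 | 0.855 | 0.94 | 6.6% |
| 0.5, 0.5, 0.7 | 11.232 | 12.960 | 0.759 | 0.815 | 0.93 | 6.8% |
| 0.5, 0.4, 0.7 | 12.096 | 15.552 | 0.788 | 0.893 | 0.88 | 8.4% |
| 0.4, 0.3, 0.7 | 13.824 | 18.144 | 0.842 | 0.965 | 0.87 | 8.7% |
| 0.4, 0.6, 0.4 | 13.824 | 10.368 | 0.842 | 0.729 | 1.15 | 2.4% |

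The last row has baseline and 3 months as the most alike pair. Its interval is too wide, with coverage 97.6%.

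**Simulation check.** Runs of 20,000 trials with 39 per arm agree. Coverage was 92.9% for 0.5, 0.5, 0.7 and 97.4% for 0.4, 0.6, 0.4. Type I error was 8.5% for 0.5, 0.4, 0.7 and 8.9% for 0.4, 0.3, 0.7. In a set of five correlation patterns that included the equal, 0.5, 0.5, 0.7 and 0.4, 0.6, 0.4 cases, estimating the contrast's own variance gave coverage of 94.8–95.2% throughout.

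**1-month change.** The same pooled M is used here too. With 0.5, 0.5, 0.7 the 1-month interval is also too narrow (93.2%). With correlations that decay in time (0.6, 0.36, 0.6) it is too wide (96.8%), while the 3-month interval is too narrow (91.0%).

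**Unequal variance.** With all correlations 0.5 and SDs of 4.2, 3.6 and 3.0, coverage for the 3-month change is 94.6%. For this contrast the correlation pattern drives the result far more than unequal variance does.

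**The case against.** The best case against the point has four parts.

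- **The structure may be incomplete, not wrong.** The article names a random intercept but does not say that it is the only covariance term or that residuals are independent. Residual covariance is a detail that a condensed article commonly leaves to the SAP. This stands as a limit: compound symmetry is the usual reading of the stated model, but it is a reading.
- **The primary interval comes from elsewhere.** A reader might infer that the primary result carries a 7–9% false-positive rate. The Statistical analysis section does not support that, because it assigns the primary mean difference and its 95% CI to ANOVA and adds the mixed model for change over time. The abstract's wording keeps the point relevant to between-group intervals but does not turn these rates into the error rate of the primary analysis.
- **There is a safeguard.** Robust methods are promised if assumptions fail, and cluster-robust standard errors would fit that description. But the listed mixed-model checks are linearity, residual normality and homoscedasticity. None of them examines correlation over time, so this fault need not trigger the remedy. The protection is partial.
- **The direction is assumed.** A reader might infer that the interval is bound to be too narrow. The documents give no correlations, and the 0.4, 0.6, 0.4 case goes the other way. Nor does a closer 1-to-3-month pair by itself give 8–9%; with 0.5, 0.5, 0.7 it gives about 7%. The larger figures also need a lower baseline–3-month correlation.

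The restriction to equal correlations has no effect on self-management behaviour or EQ-5D-5L, which have only two visits.

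**Conclusion.** The point holds as a moderate weakness of specification. As stated, and with the usual independent residuals, the longitudinal model for the CADE-Q SV and the ACS Response Index ties its interval for change to an equal-correlation assumption that the design makes doubtful and that no listed check would test.

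Under the more plausible direction (follow-ups more alike than either is to baseline), type I error for the 3-month change is about 7%, and 8–9% if the baseline–3-month correlation is clearly the lowest. Under the opposite pattern the interval is too wide. These sizes rest on assumed correlations, complete data, 39 per arm and equal SDs. The SAP may already settle the matter, so this is a recommended improvement and not a demonstrated error.

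**What to change.** For the continuous outcomes measured at three visits, replace the random intercept with an unstructured 3×3 within-patient covariance, treat visit as categorical and use Kenward-Roger degrees of freedom. Report the 1-month and 3-month group contrasts from that model. If it does not converge, keep the random intercept and use small-sample-corrected cluster-robust standard errors. State this as the planned rule and do not make it depend on a diagnostic check. If the SAP already says so, no change is needed.

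The cost is one line in the SAP. An unstructured covariance has six parameters (three variances and three correlations) against two for the random-intercept model, so four more, which 98 patients can support. If equal correlation is in fact true, the interval will be slightly wider than necessary.

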**Key secondary outcomes**				
Self-management behaviours	CADSMS	✓		✓
Cardiac-related hospital admission	Self-reported or family reported		✓	✓
Healthcare service utilisation	Self-reported		✓	✓

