#### Self-management behaviours

Participants’ CHD self-management behaviours will be measured 3 months posthospital discharge using the Coronary Artery Disease Self-Management behaviour Scale. This 27-item questionnaire has three subdomains, including emotional self-management behaviours, daily life self-management behaviours and medical self-management behaviours. Participants rate each item on a 5-point Likert scale, for a total score ranging from 27 to 135, with a higher score indicating better self-management behaviours. The questionnaire was originally developed and validated in Chinese patients with CHD.^36^

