#### Quality of life

Quality of life will be measured 3 months posthospital discharge using the Five-Level EuroQol five-dimension instrument (EQ-5D-5L) (Simplified Chinese).^37^ Participants will be assessed across five health dimensions, including mobility, self-care, usual activities, pain/discomfort and anxiety/depression, based on five response categories from level 1 to 5 corresponding with no problem, slight problems, moderate problems, severe problems and extreme problems, respectively.^38^ Alongside the five health dimensions, the EQ visual analogue scale will be used to assess participants’ ‘own health today’ with end points labelled ‘best imaginable health state’ (100) and ‘worst imaginable health state’ (0). The EQ-5D-5L has been validated in Chinese populations.^37^

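### Self-management and quality of life have a single follow-up value; the planned model of between-group change, as usually fitted, is a change-score test and is less precise than adjusting for baseline

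*Protocol article*

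**What the plan says.** Table 1 of the protocol article lists "Self-management behaviours" (CADSMS) as a key secondary outcome and "Quality of life" (EQ-5D-5L) among the other secondary outcomes. Each is marked at baseline and 3 months, with nothing at 1 month. The sections describing the instruments agree on the single follow-up: "CHD self-management behaviours will be measured 3 months posthospital discharge" and "Quality of life will be measured 3 months posthospital discharge".

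The Statistical analysis section describes a mixed model twice.

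- For the primary outcome, besides the ANOVA, "a linear mixed effects regression model will be used with a random intercept for patients to account for individual variability". The question put to that model is "change in the outcome over time (baseline, 1 month and 3 months) within and between groups", so baseline is one of the levels of time.
- For the secondary outcomes: "For secondary continuous outcomes, linear mixed effects regressions will be performed to assess whether there is change in the outcomes over time within and between" the arms. No fixed-effect terms and no baseline covariate are named.

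The abstract adds that between-group comparisons are made "accounting for baseline differences using linear mixed effects or mixed effects logistic regression models". The article also refers to a prespecified statistical analysis plan, which is not shown.

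**The concern.** A patient-level mixed model needs more than one row per patient. For CADSMS and EQ-5D-5L there is one post-discharge value, so baseline has to be a response row; otherwise a patient intercept cannot be separated from residual error and change within groups cannot be estimated. The usual model then has group, time and group-by-time terms, and the between-group question is answered by the interaction. That interaction subtracts each patient's baseline in full, with the slope fixed at 1, instead of using the slope that the data support.

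What is at stake is precision on a key secondary behavioural outcome and on quality of life, in a trial sized for about 39 evaluable patients per arm. The baseline scores that would recover the precision are already being collected.

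**Working it through.** **The plan's own figure.** The article gives no sample size or power for these two outcomes. Its only calculation is for CADE-Q SV: 2 × (1.960 + 0.842)² × 3.6² / 2.3² = 38.5, so 39 per arm and 78 in total; 78/0.8 = 97.5, so 98. This reproduces, and the present point does not affect it.

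**Inputs.** Two visits per outcome (Table 1); 39 evaluable per arm (Sample size calculation); ρ, the correlation between baseline and 3 months, is not given and is assumed over a range. Equal variance σ² at both visits is assumed.

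**Step 1: variance of the between-group estimate, in units of 2σ²/n with n per arm.**

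- Difference in mean change: 2(1−ρ)
- 3-month difference adjusted for baseline (ANCOVA): 1−ρ²
- 3-month difference ignoring baseline: 1

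**Step 2: ratio of change score to ANCOVA.** 2(1−ρ)/(1−ρ²) = 2/(1+ρ). The square root gives the relative width of the confidence interval. The inverse, (1+ρ)/2, times 39 gives the number per arm with which ANCOVA would match the change-score analysis of 39.

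| Assumed ρ | Variance ratio 2/(1+ρ) | CI width ratio | 39 × (1+ρ)/2 |
|---|---|---|---|
| 0.3 | 1.54 | 1.24 | 25.4 |
| 0.5 | 1.33 | 1.15 | 29.3 |
| 0.7 | 1.18 | 1.08 | 33.2 |
| 0.8 | 1.11 | 1.05 | 35.1 |

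Against a comparison that ignores baseline, the change score has variance 2(1−ρ): 1.4 at ρ = 0.3, 1.0 at 0.5 and 0.6 at 0.7. It is the worse of those two below 0.5 and the better above.

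**Step 3: is the mixed model really the change score?** Simulated trials of 78 patients (39 per arm, two visits, complete data, 100 data sets at each ρ) were analysed four ways. Mean standard errors in SD units:

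| ρ | Change score | Mixed model, free baseline means | ANCOVA | Mixed model, common baseline mean |
|---|---|---|---|---|
| 0.4 | 0.249 | 0.249 | 0.208 | 0.207 |
| 0.6 | 0.201 | 0.201 | 0.180 | 0.179 |
| 0.8 | 0.144 | 0.144 | 0.137 | 0.136 |

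The estimates in the first two columns agree to about 3 × 10⁻¹⁵ and their standard errors to about 4 × 10⁻⁶. The last column also has baseline as an outcome, yet it matches ANCOVA. The loss therefore comes from leaving the baseline means free.

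**Step 4: unequal variances.** With SDs σ₀ at baseline and σ₁ at 3 months, the change-score variance minus the ANCOVA variance is (σ₀² + σ₁² − 2ρσ₀σ₁) − σ₁²(1−ρ²) = (σ₀ − ρσ₁)², which is never negative. The direction of the result does not depend on the equal-variance assumption; the ratios in the table do.

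**The case against.** The strongest reply is that the article does not fix the model criticised. It gives no fixed-effect terms for the secondary outcomes, states the random intercept only for the primary-outcome model, and points to an analysis plan that is not shown. A mixed model with a common baseline mean also assesses change within and between groups, so the efficient analysis is compatible with the quoted sentence, and the abstract says that baseline is taken into account. All of this stands, and it limits the point to the usual form of the stated model. It does not remove it. The common-mean constraint has to be imposed deliberately and nothing in the article does so. The abstract's wording does not say how, and full subtraction of baseline would also satisfy it.

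The exact equality needs complete data. With dropout, a mixed model also uses patients who have only a baseline value. The article plans multiple imputation for data missing at random; where that is applied, the equality holds within each completed data set.

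Three stronger readings are tempting, and the documents do not support them.

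- A reader might infer that the contrast is biased. Under randomisation it is unbiased; only its precision is at issue.
- A reader might infer that using baseline as an outcome is itself the fault. The last column of the simulation table shows otherwise.
- A reader might convert the loss into power for CADSMS with the effect of 2.3 on an SD of 3.6. Those figures belong to CADE-Q SV, a different instrument, and are described as a mean change with its SD, so 3.6 may already be an SD of change. The article gives no effect, SD or correlation for CADSMS or EQ-5D-5L.

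**Conclusion.** The point holds as one of efficiency. In the usual parameterisation, the stated analysis of CADSMS and EQ-5D-5L is a comparison of change scores, with variance 2/(1+ρ) times that of a baseline-adjusted comparison: 1.54, 1.33 and 1.18 at ρ of 0.3, 0.5 and 0.7. The loss is small if ρ is high (1.11 at 0.8).

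This rests on free baseline means, complete or completed data, equal variances at the two visits and an assumed ρ. Baseline is taken in hospital after an acute event, which makes a modest ρ conceivable, but nothing in the documents shows it. The primary outcome and the sample size are not affected. It is a worthwhile, nearly free improvement, not a flaw that threatens the trial's conclusions.

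**What to change.** State in the Statistical analysis section or the analysis plan that, for CADSMS and the EQ-5D-5L scores, the between-group result is the 3-month difference with its 95% CI, adjusted for the baseline score of the same measure (ANCOVA). Alternatively, keep the linear mixed model but constrain the arms to a common baseline mean: time and group-by-time terms, no group effect at baseline, and an unstructured 2×2 covariance. The second form also keeps patients who have only a baseline value. Within-group change can still be shown descriptively.

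The cost is one changed model statement and one degree of freedom, with no new data, visits or patients. The result would be labelled an adjusted 3-month difference instead of a difference in change; under randomisation both estimate the same quantity. Adding baseline to the primary-outcome ANOVA would not deal with these two outcomes, so they need their own sentence.
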